**Methods and analysis:**

The aim of this 5-week randomised, sham-controlled, double-blinded pilot clinical trial (n=72) is to assess the underlying mechanisms of action of iTBS in females in the late menopause transition and the relationship with cognition and mood. Data will be analysed using Stata^TM^. Normality checks will guide the choice between parametric and non-parametric tests. Generalised linear models will assess within-subject and between-subject effects across timepoints, with additional regression analyses exploring associations between biomarkers, cognition and mood. Effect sizes, CIs and relevant test statistics will be reported, with significance set at p<0.05.

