### Objectives and Trial Design

Despite research demonstrating that iTBS may have clinical utility in treating cognitive and mood changes, no such study has been conducted to explore the potential of iTBS to modulate the neurophysiological changes that can underpin cognitive and mood changes during the menopause transition. Such data are essential in identifying potential mechanisms by which to treat or prevent cognitive decline during this transition. The objective of this randomised, sham-controlled, double-blinded pilot clinical trial is to assess the underlying mechanisms of action of iTBS in females in the late menopause transition and to assess the relationship with cognition and mood.

A pilot trial design was selected due to the novelty and exploratory nature of the research question; and to assess the intervention mechanisms to determine whether the protocol will be viable in future studies that would explore treatment efficacy as the primary outcome.

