### Outcomes

All outcomes were assessed at three time points and full details of the outcome measures are outlined in table 1. As this is a pilot clinical trial, primary outcomes are mechanistic and include cortical activity, assessed via electroencephalography (EEG). Paired-pulse TMS will be used to investigate activity within intracortical circuits as a co-primary outcome. Intracortical inhibition will be measured via short-interval intracortical inhibition (SICI) and long-interval intracortical inhibition (LICI).

**Table 1 T1:** Schedule of Activities

Activity	Online Screening	Phone Screening	Baseline	Endpoint	Follow-Up
Inclusion and Exclusion Criteria	X	X			
FSH Pathology		X			
TMS Adult Safety Screen Questionnaire		X			
Telephone Montreal Cognitive Assessment		X			
EEG Measures			X	X	X
TMS Measures			X	X	X
Heart Rate Variability			X	X	X
Skin Conductance			X	X	X
Saliva Collection			X	X	X
Urine Collection			X	X	X
Memory and Cognitive Confidence Scale			X	X	X
Rey Auditory Verbal Learning Test			X	X	X
D-KEFS Verbal Fluency			X	X	X
Symbol Digit Modality Test			X	X	X
Paced Serial Addition Test			X	X	X
Conners Continuous Performance Test-3			X	X	X
Visual Analogue Scale to Evaluate Fatigue Severity			X	X	X
Patient Health Questionnaire-9		X	X	X	X
General Anxiety Disorder-7			X	X	X
Pittsburgh Sleep Quality Index			X	X	X
Menopause-Specific Quality of Life			X	X	X

D-KEFS, Delis-Kaplan Executive Function System; EEG, Electroencephalogram; FSH, Follicle Stimulating Hormone; TMS, Transcranial Magnetic Stimulation.

Secondary outcomes include changes in subjective cognitive complaints and objective changes in verbal memory, verbal learning, verbal fluency, psychomotor processing speed, working memory, and sustained attention and vigilance. The clinical trial will also assess the effects of an rTMS intervention on the psychological symptom profile as secondary outcomes, including depressive mood, anxiety, sleep quality, and quality of life.

Tertiary outcomes include changes in autonomic function, which will be assessed via skin conductance and heart rate variability (HRV). Changes in inflammatory and energetic markers and neuroactive metabolites will be measured via saliva and/or urine analysis.

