#### Biochemical Outcomes

The biospecimen collection and processing protocol, biochemical outcomes, and analyses plans are outlined in online supplemental material 2.

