### Statistical Methods

A data-driven approach will be applied to de-identified data in Stata^TM^ (StataCorp, Texas, USA). Normality checks will be performed for all variables via visual inspection of histograms to determine whether parametric or non-parametric approaches should be used. Two-tailed independent group *t*-tests with equal variances assumed will be used for all continuous variables, and χ^2^ tests will be conducted for categorical variables. Dependent variables taken at baseline and all following timepoints will be analysed for within-subject and between-subject comparisons using generalised linear models with planned simple contrasts for the within-subjects factor of time. To determine the relationship between immunological, bioenergetic and neuroimmune biomarkers and changes in cognition and mood, a logistic regression analysis will be performed.

A possible signal of efficacy will be explored via effect-size estimates of changes in tertiary outcomes (cognition and mood). Effect sizes, means, SDs and CIs will be reported. Normality checks will be performed, and data will be transformed if necessary. Where appropriate, parametric tests will be applied. A generalised linear model with fixed and random effects will be applied for the tertiary outcomes. Variables will include the between-subjects factor of group (active vs sham) and within-subjects factor of time (baseline, endpoint and follow-up). Pearson correlation coefficients (or their non-parametric counterpart) or multivariate regression involving tertiary outcomes will be conducted. All tests will be carried out one-tailed and using an alpha level of 0.05.

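### The analyses linking biomarkers to cognition and mood state no treatment-group term, and one named option cannot hold one; if pooled, a shared iTBS effect can look like a link or hide one

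*Protocol article*

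**What the plan says.** The trial's aim is given under Objectives and Trial Design: "to assess the underlying mechanisms of action of iTBS in females in the late menopause transition and to assess the relationship with cognition and mood". Two sentences in Statistical Methods serve the relationship part of that aim.

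- The first names the variables and the model: "To determine the relationship between immunological, bioenergetic and neuroimmune biomarkers and changes in cognition and mood, a logistic regression analysis will be performed". It states no covariates, no binary outcome, and no choice between baseline biomarker levels and biomarker changes.
- The second is looser: "Pearson correlation coefficients (or their non-parametric counterpart) or multivariate regression involving tertiary outcomes will be conducted". It names no pair of variables. The Outcomes section places autonomic and biochemical measures in the tertiary tier, while Statistical Methods glosses that tier as cognition and mood.

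Treatment group is named as a model factor in one place, the sentence between the mixed model for tertiary outcomes and the correlation sentence: "Variables will include the between-subjects factor of group (active vs sham) and within-subjects factor of time (baseline, endpoint and follow-up". Because it pairs group with the repeated factor of time, it reads most naturally as part of that model.

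The abstract describes the association analyses as exploratory ("with additional regression analyses exploring associations between biomarkers, cognition and mood"). The biochemical analysis plans are referred to a supplement that is not shown ("The biospecimen collection and processing protocol, biochemical outcomes, and analyses plans are outlined in online supplemental material 2").

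**The concern.** For a mechanistic question, the useful null hypothesis is that a woman's biomarker tells us nothing about her cognitive or mood change once we know her arm. A correlation or regression over all women without group tests a different null: no marginal association in a 2:1 mixture of active and sham participants. Randomised arm is a cause of both variables when iTBS affects both. The marginal null is then false even if the two are unrelated among women in the same arm.

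In that case the association analysis repeats what the between-group comparisons already show, but looks like evidence of a link between marker and symptom. The reverse can also occur. If iTBS moves a marker and a score in opposite directions while they are positively related within arms, pooling pulls the correlation toward zero. The risk is greatest in the scenario the trial hopes for, where iTBS changes both markers and symptoms.

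**Working it through.** **Inputs from the protocol article.** Sample size before dropout: 60 (Sample Size Determination). Allocation: 2:1 active to sham (Allocation), so 40 and 20, with active fraction p = 2/3. Alpha: 0.05. Statistical Methods ends by making all tests one-tailed but earlier specifies two-tailed t-tests, so both are shown. The article gives no figure for these association analyses, so there is none to reproduce.

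**Assumed inputs.** The treatment shifts d1 and d2, in within-arm SD units, and the within-arm correlation ρ. The article gives none of them, so a range is used.

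**Pooled correlation.** With v = p(1 − p) = (2/3)(1/3) = 0.222:

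r = (ρ + v·d1·d2) / √[(1 + v·d1²)(1 + v·d2²)]

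For ρ = 0 and equal shifts d this becomes r = v·d² / (1 + v·d²):

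- d = 0.3: 0.020/1.020 = 0.020
- d = 0.5: 0.0556/1.0556 = 0.053
- d = 0.8: 0.1422/1.1422 = 0.125
- d = 1.0: 0.2222/1.2222 = 0.182

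If d1 or d2 is zero, the numerator is zero and there is no distortion.

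**False-positive rate of the pooled Pearson test** (simulated, bivariate normal, ρ = 0, 40 vs 20, t-test on 58 df):

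| Shift in both variables | One-tailed | Two-tailed | With group in the model |
|---|---|---|---|
| 0 | 5% | 5% | 5% |
| 0.3 SD | 7% | 5.5% | 5% |
| 0.5 SD | 11% | 7% | 5% |
| 0.8 SD | 24–25% | 16% | 5% |
| 1.0 SD | 41% | 29% | 5% |

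The simulated mean correlations (0.020, 0.053, 0.125, 0.183) match the formula. If all 72 women contribute, the one-tailed rates are 7%, 12%, 28% and 46% at the four non-zero shifts.

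**The logistic regression.** No binary outcome is named, so the change score was split at its median, which is a further assumption. Without group, one-tailed rejection is about 9%, 19% and 31% at 0.5, 0.8 and 1.0 SD. With group it is close to 5%. The pattern is the same and somewhat weaker.

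**Hiding a real link.** With ρ = 0.3 and opposite shifts of 0.8 SD, the pooled correlation is (0.3 − 0.142)/1.142 = 0.138. One-tailed power at 60 women is 27% pooled and 76% adjusted for group.

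**Cost in power.** With no treatment effect and ρ = 0.35, one-tailed power is 87% with or without group in the model. This covers adjustment for group only; baseline covariates were not simulated.

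**The case against.** The strongest reply is that the article never says the arms are pooled or that group is left out. A reader might infer from the text that the relationship is tested without treatment group and that a false mechanism will be reported. The document does not support that. The regression covariates are simply unstated, correlations could be run within arm, and the supplement with the biochemical analysis plans is not shown. Covariate lists for exploratory models are often left to a fuller document.

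Other parts of the reply also stand:

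- The correlation sentence does not name biomarkers against cognition or mood; the logistic regression sentence does.
- That sentence does not say the biomarkers are changes. Baseline levels would be independent of arm by randomisation, and the distortion would not arise.
- The inflation is small at 0.3 SD and serious only from about 0.8 SD in both variables.
- A pooled test detects a true marginal association. The error lies in reading it as a within-arm link, and no passage commits to that reading or ties a decision to these p-values.

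What the reply does not remove is that the article names a method, the simple correlation, which cannot include group. The single mention of group sits with the repeated-measures model. For a trial with a mechanistic aim, this is a choice of method that can be improved, and so more than an omitted detail.

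**Conclusion.** The point holds in a conditional form. As written, the logistic regression carries no stated group term and the correlation option cannot carry one. If they are run on the pooled arms with post-treatment or change values, and iTBS shifts both variables, the result mixes a shared treatment effect with any within-arm association. At 60 women and 2:1 allocation, the one-tailed false-positive rate of the pooled correlation is close to nominal at 0.3 SD, about double at 0.5 SD, about five times at 0.8 SD and about eight times at 1.0 SD. Two-tailed rates are lower, at most 29% over this range. All these shifts are assumptions. The change is worth making because it serves the stated aim at little cost, but the text does not show that a false mechanism would be reported.

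**What to change.** In Statistical Methods:

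1. State whether the biomarker variable is a baseline level or a change.
2. Include treatment group in every regression of cognitive or mood change on biomarker change, and adjust for the baseline values of both where the sample allows.
3. Replace the whole-sample Pearson or rank correlation with a group-adjusted partial correlation (for ranks, a partial Spearman) and its CI, or report the correlation within each arm.
4. Label any unadjusted whole-sample correlation as descriptive.

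The cost is a few sentences, one degree of freedom for group and one for each baseline covariate. No new data are needed.

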### Sample Size Determination

An exploratory sample size of 60 participants has been chosen to maximise feasibility and recruitment potential and characterise the potential mechanisms of iTBS in this pilot clinical trial. This sample size was calculated using the following calculator for binary sample sizes: https://www.johndcook.com/binary_sample_size.html. The calculator is based on the rule of thumb which assumes significance α=0.05 and type II error β=0.20 (80% power). We are assuming a potential dropout rate of 20% based on previous clinical trial experience,^24^ which requires an additional 12 participants (72 total).

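### The Statistical Methods section makes t-tests two-tailed and then makes all tests one-tailed at 0.05, leaving two different significance rules for the same outcomes

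*Protocol article*

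**What the plan says.** Two sentences in the Statistical Methods section of the protocol article set sidedness.

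- First paragraph: "Two-tailed independent group *t*-tests with equal variances assumed will be used for all continuous variables".
- End of the second paragraph: "All tests will be carried out one-tailed and using an alpha level of 0.05".

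No sentence says which tests follow which rule, names a favoured direction for any test, or gives a reason for one-tailed testing.

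Two other places give a significance level without sidedness. The abstract (Methods and analysis) says "Effect sizes, CIs and relevant test statistics will be reported, with significance set at p<0.05". The Sample Size Determination section says its calculator "assumes significance α=0.05 and type II error β=0.20 (80% power". Both fit either rule, so neither settles the matter.

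**The concern.** Both sentences are universal, one over continuous variables and the other over tests. A t-test on a continuous outcome falls under both and cannot obey both.

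Three things are at stake. First, a favourable result of intermediate strength can be called significant or not depending on which sentence the analyst follows. Second, a one-tailed test needs a tail fixed in advance. For the co-primary measures (EEG activity, SICI and LICI), the biomarkers and the correlations, the article states no direction. Third, a one-tailed test toward benefit cannot declare a change for the worse. The stated objective is to learn how the stimulation acts, and there an effect in the unexpected direction is as informative as one in the expected direction.

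**Working it through.** **Step 1. Which outcomes fall under both rules?**

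| Reading of the last sentence | Outcomes under the one-tailed rule | Also under the two-tailed rule? |
|---|---|---|
| Literal: all tests in the trial | Every outcome, including EEG and SICI/LICI | Yes, for every continuous variable compared by t-test |
| Narrow: second paragraph only | Cognition and mood, which that paragraph labels tertiary | Yes, because these scores are continuous |

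The conflict shrinks under the narrow reading but does not disappear. The χ² tests in the first paragraph are ordinarily non-directional, so a rule that makes all tests one-tailed also fits them badly.

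**Step 2. Size of the difference in error rate.** The probability of a false positive in the favoured direction is 1 − Φ(critical z).

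- Two-tailed at 0.05: critical z = 1.960, so 1 − Φ(1.960) = 0.025.
- One-tailed at 0.05: critical z = 1.645, so 1 − Φ(1.645) = 0.050.
- Ratio: 0.050 / 0.025 = 2, exactly.

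A one-tailed test would need alpha 0.025 to keep the same error in the favoured direction as a two-tailed test at 0.05.

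**Step 3. The band of results affected.** The Sample Size Determination section gives 60 participants before the dropout allowance, and the Allocation section gives 2:1 active to sham, hence 40 and 20. With 40 + 20 − 2 = 58 degrees of freedom the critical t is 2.002 two-tailed and 1.672 one-tailed. A favourable t between 1.672 and 2.002, which is a two-sided p between 0.10 and 0.05, is significant under the last sentence and not under the first paragraph.

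**Step 4. What a two-sided rule costs (illustration only).** The article states no effect size, SD or event rate, and the calculator it names is for binary outcomes, so there is no detectable effect of its own to reproduce. Assume a simple two-sample t-test, 40 versus 20, 80% power. By the normal approximation, d = (z for alpha + 0.842) × √(1/40 + 1/20), and √(1/40 + 1/20) = 0.274.

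- Two-sided: (1.960 + 0.842) × 0.274 = 0.77 SD.
- One-sided: (1.645 + 0.842) × 0.274 = 0.68 SD.

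The exact noncentral-t calculation gives 0.78 and 0.69 SD. These figures describe a t-test, not the planned repeated-measures model.

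**The case against.** The strongest reply is that the two sentences have different scopes. The one-tailed sentence closes a paragraph about exploring an efficacy signal in cognition and mood, and the two-tailed sentence sits in a paragraph about general comparisons. On that view the primary outcomes are never tested one-tailed. This is a fair reading and it stands as a limit: one cannot say with certainty that the one-tailed rule reaches EEG, SICI or LICI. It does not remove the conflict, because cognition and mood scores are continuous variables too, and the last sentence carries no words that restrict it.

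A second reply is that the direction is obvious. For cognition and mood this largely stands. The abstract, the Introduction and the Discussion all speak of improvement, so benefit is the implied tail. A reader might infer that the tail could be picked after seeing the data, with a total error of 2 × 0.05 = 10%. For cognition and mood the article does not support that. For the mechanistic outcomes, biomarkers and correlations no direction is implied, and 10% would arise only if the one-tailed rule covers them and the tail were in fact chosen late.

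A third reply is that this is a pilot. The Discussion says efficacy conclusions are limited, and the efficacy signal is to be explored through effect-size estimates, whose values do not depend on the tail. That lowers the severity. It does not make the point idle, because the abstract still commits to a significance threshold.

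Two further inferences are not supported. The article promises confidence intervals without giving their level or sidedness, so one cannot say that its tests and intervals disagree. It also states no detectable effect, so a two-sided rule worsens no figure that it gives.

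**Conclusion.** The section is wrong as written: it contains two incompatible rules on sidedness and nothing elsewhere in the article chooses between them. It would go too far to say that the trial's false-positive rate is undefined. Nominal alpha is 0.05 under both rules; what is left open is the rate in the favoured direction, 2.5% or 5%. The doubling is exact but conditional: it applies only in the favoured direction and only where the one-tailed sentence governs.

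The reach is every outcome on the literal reading, and at least the continuous cognition and mood scores on the narrow one. The error rates need no assumption beyond standard test theory; the t critical values assume 40 versus 20 participants analysed. The point should be fixed rather than treated as critical, since the trial is an exploratory pilot and the article ties no confirmatory decision to these tests.

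**What to change.** Replace the last sentence of the Statistical Methods section with: *All tests are two-sided at alpha 0.05 and are reported with two-sided 95% CIs.* Apply it to primary, secondary and tertiary outcomes and to the correlations. This agrees with the section's own first paragraph and should be settled before unblinding.

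Stating sidedness once for each family of tests, with the direction and a reason wherever a test is one-tailed, would also remove the contradiction. The single two-sided rule is simpler and allows worsening to be declared.

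The cost is one sentence and somewhat lower power in the favoured direction, of the order of 0.78 rather than 0.69 SD detectable in the illustration above. No extra participants or data are needed.

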## DISCUSSION

This randomised, sham-controlled, double-blinded pilot trial will explore the neurophysiological, cognitive and mood effects of non-invasive brain stimulation during the late menopause transition. Building on prior research, it aims to address the evidence-practice gap in managing cognitive and mood symptoms via non-pharmacological methods.

As the first study of its kind, an exploratory sample size was selected based on previous mechanistic studies stimulating the DLPFC in healthy individuals, as well as rTMS/iTBS pilot trials reporting cognitive improvements in clinical populations (sample sizes typically 10–30). While efficacy conclusions are limited by the pilot design, the sample size allows for subgroup analyses of mechanistic outcomes. Mechanistic changes were prioritised as primary outcomes due to the exploratory nature of the study and the need to assess protocol feasibility for future efficacy trials. Results will also inform effect size estimates for adequately powered future studies.

Findings from this pilot clinical trial have the potential to advance our understanding of the underlying mechanisms that affect cognition and mood in menopause and offer the potential for new non-invasive treatments to mitigate symptoms. The successful implementation of this pilot trial could inform future trials and offer a scalable intervention to improve cognition and mood in females experiencing the late menopause transition.

## ETHICS AND DISSEMINATION

### Ethics Approval

The study protocol has been reviewed and ethically approved by the Western Sydney University Human Research Ethics Committee (H16200; 8 November 2024). Participants will be directly consented by the investigator via oral and electronic written consent. The Participant Information Sheet and Consent Form is available as online supplemental material 3. Procedures have been designed to minimise participant risk and burden, and all study activities will be conducted in accordance with the National Statement on Ethical Conduct in Human Research and relevant institutional and legal guidelines.

